### Power analysis

The power calculation is based on our primary outcome hot flush score. The software G*Power was used to calculate the sample size a priori [42]. Since no OLP study has been conducted in the field of hot flushes, we base our sample size calculation on two separate clusters of information. From double-blind hot flush trials we can expect a moderate effect size of Cohen’s *d* = 0.40 given a mean of 19, standard deviations of 10 [23], and a four-point reduction in the hot flush score (frequency × severity) after 4 weeks of placebo [43]. Based on previous OLP trials in patients with irritable bowel syndrome and chronic low back pain, a large effect size of *d* = 0.80 can be expected [28, 30]. Combining these two clusters of information, a moderate to large effect size is expected for the difference between the OLP and the no-treatment groups at post-treatment. For a two-tailed Student’s *t*-test with an *α*-error rate of 0.05, a number of *N* = 90 participants would provide an 80% power to detect an effect of *d* = 0.60. We assumed an attrition rate of 10% and obtained our required sample size of *n* = 100 women.

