### Statistical analyses

All hypotheses are tested two-sided with an *α*-level of 0.05.

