#### Efficacy

For our primary outcome hot flush composite score, we conduct a linear mixed model for repeated measures using restricted maximum likelihood estimations with the intent-to-treat sample. We define group membership (OLP/no treatment), measurement point, and their interaction term as fixed effects. The baseline score is additionally included as a covariate. Measurement points are treated as repeated measures with an autoregressive residual covariance structure. Moreover, the model includes a random intercept to model between-subject differences. A normal distribution with an identity link is used. Since each data point reflects a weekly mean, up to five weekly means are included for each participant. Effect sizes are obtained by dividing the estimated group difference by the product of standard error by square root of the number of participants in the no-treatment group [68]. For our primary outcome bothersomeness of hot flushes, we will perform a linear mixed model with two data points at baseline and post-treatment. A post-hoc test comparing OLP with no-treatment will be conducted to test the group difference at post-treatment.

By fitting (generalized) linear mixed models, the analytical strategy for all secondary outcomes corresponds with the one described for the primary outcome. For metric outcomes (health-related quality of life and global improvement) we use a normal distribution with an identity link. For dichotomous outcomes (response), we use a binomial distribution with a logit link, and for count outcomes (hot flush frequency), we use a negative binomial distribution with a log-link.

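### The model for the primary outcome bothersomeness enters baseline as an outcome row and states no baseline covariate, so its week-4 contrast is less precise than the collected data allow

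*Protocol article*

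**What the plan says.** The Efficacy section describes the composite-score model in full: group, measurement point and their interaction as fixed effects, a random intercept and an autoregressive residual structure. It then says of baseline: "The baseline score is additionally included as a covariate".

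For the second primary outcome the description is short: "For our primary outcome bothersomeness of hot flushes, we will perform a linear mixed model with two data points at baseline and post-treatment". The test is given as: "A post-hoc test comparing OLP with no-treatment will be conducted to test the group difference at post-treatment". Fixed effects, a baseline covariate and a common baseline mean are not mentioned for this outcome, and none of them is ruled out.

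The Power analysis section covers only one of the two primary outcomes: "The power calculation is based on our primary outcome hot flush score". It uses an unadjusted two-sample t-test. No standard deviation, effect size or baseline-post correlation is given for bothersomeness.

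**The concern.** Bothersomeness has one baseline and one post-treatment value per woman. In a two-row mixed model with group, time and group × time, each arm has its own free mean at each time. With complete data, the post-treatment contrast is then simply the difference between the two week-4 means. The baseline score is in the data set but does nothing for the primary contrast. If the arms differ by chance at baseline, that difference passes into the estimate in proportion to r.

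Two things are at stake: precision that the trial could have at no cost, and exposure of a primary estimate to chance imbalance. The Randomization section states permuted blocks for the first allocation and names no stratification factor, so the design does nothing to balance baseline bother. The two primary outcomes may also be handled differently with respect to baseline without a stated reason.

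**Working it through.** **Inputs from the article**
- Two-sided α of 0.05 (Statistical analyses: "All hypotheses are tested two-sided with an" α-level of 0.05).
- 1:1 allocation (Study design).
- N = 90 evaluable, so 45 per arm, and d = 0.60 (Power analysis: N = 90 "participants would provide an 80% power to detect an effect of" d = 0.60). The value 0.60 is the midpoint of the article's two benchmarks: (0.40 + 0.80)/2.
- 10% attrition ("We assumed an attrition rate of 10% and obtained our required sample size of" 100).

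**Assumptions, because the article gives no figure**
- d = 0.60 is borrowed from the composite score.
- r, the baseline-post correlation of bothersomeness, is shown from 0.3 to 0.7.

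**1. The plan's own figure.** Noncentral t with noncentrality d·√(n/2) = 0.60 × √22.5 = 2.85 and 88 df gives power of 80.4%. Forty-five per arm is the smallest size that reaches 80%. Then 90/0.90 = 100. The plan's figures reproduce.

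**2. What the two-point model estimates.** REML fits with a random intercept and group × time were run on 150 simulated trials (45 per arm, r = 0.5). With complete data, the week-4 contrast equalled the raw difference in week-4 means to about 1e-15. With 10% of post scores missing it departed from the raw difference by up to 0.12 SD, because baseline then informs the missing values.

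**3. Power with baseline as covariate.** Residual variance falls by the factor 1 − r². The effective effect is 0.60/√(1 − r²), with 87 df.

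| r | 1 − r² | effective d | power | gain over 80.4% |
|---|---|---|---|---|
| 0.3 | 0.91 | 0.629 | 83.9% | 3.5 points |
| 0.4 | 0.84 | 0.655 | 86.7% | 6.3 |
| 0.5 | 0.75 | 0.693 | 90.1% | 9.8 |
| 0.6 | 0.64 | 0.750 | 94.0% | 13.7 |
| 0.7 | 0.51 | 0.840 | 97.6% | 17.3 |

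The gain also depends on d. At r = 0.5 it is 11.5 points for d = 0.40 (46.7% to 58.2%) and 2.8 points for d = 0.80. In a separate simulation of 4000 trials at r = 0.5 and d = 0.60, power was 80.6% for the planned contrast and 90.3% for ANCOVA.

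**4. Chance imbalance.** In SD units the standard error of the baseline difference is √(2/45) = 0.211. A difference of at least 0.2 SD therefore arises in about 34% of randomisations (z = 0.2/0.211 = 0.95). At r = 0.5 a 0.2 SD difference moves the raw contrast by 0.5 × 0.2 = 0.1 SD, one sixth of d = 0.60. In the 150 complete-data simulations the planned estimate correlated about 0.44 with the baseline difference, and the ANCOVA estimate about −0.09. The first correlation did not go away with 10% missing post scores.

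**5. If the composite model's covariate carries over.** Baseline is then both an outcome row and a covariate with one common slope. That slope averages 1 (baseline on itself) and r (post on baseline), so b = (1 + r)/2. The variance relative to the raw contrast is 1 + b² − 2br:
- r = 0.5: b = 0.75, and 1 + 0.5625 − 0.75 = 0.81, against 0.75 for ANCOVA. Power is about 87.8%.
- r = 0.3: b = 0.65, and 1 + 0.4225 − 0.39 = 1.03, against 0.91 for ANCOVA. Power is about 79.1%, slightly below no adjustment.

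**The case against.** - **The missing covariate is inferred from silence.** The bothersomeness sentence is brief and follows the full composite model. If it inherits that model's fixed effects, it may inherit its baseline covariate too. Up to five weekly means over a four-week treatment suggests that the composite model itself has baseline as both outcome and covariate. This stands: the text is under-specified and does not expressly exclude adjustment. It does not remove the point, because step 5 shows that the inherited form is also inferior to ANCOVA.
- **Nothing falls below plan.** This stands. The trial was sized with an unadjusted t-test, and the two-point contrast delivers that power at the planning inputs. A reader might infer that the primary test is biased or underpowered against its target. The article does not support that: under randomisation the raw contrast is unbiased, and its standard error already allows for chance imbalance.
- **A loss of about 10 points is not the article's figure.** This stands. It needs r = 0.5, which is not given, and d = 0.60, which was derived for another outcome. The entry cut-off on bother (sum score of at least 16) narrows the baseline range and may lower r.
- **Women with baseline only are not useless in the planned model.** This stands when post scores are missing (step 2), and it bears on the choice of replacement.
- **An article may leave covariate lists to fuller documents.** This stands only in part. The article does fix the data structure and the test for this primary outcome, and followed as written they give the less precise contrast.

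**Conclusion.** The point holds as a free improvement to a primary analysis. On either reading of the bothersomeness sentence, the week-4 contrast uses the baseline score less well than it could: not at all with complete data and free baseline means, or with too steep a slope if the covariate is inherited.

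Against the unadjusted reading, the gain from proper adjustment is about 3.5 to 17 points of power for r from 0.3 to 0.7, on borrowed inputs of 45 per arm and d = 0.60. The lower part of that range is more plausible if the entry cut-off reduces r. The planned 80% is not missed and the test is valid. What is forgone is precision, and protection of the estimate against chance baseline imbalance.

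**What to change.** State one model for bothersomeness before the data are analysed, in either form:
- ANCOVA: week-4 bother score on group and baseline bother score, with the group coefficient as the primary test; or
- the two-point mixed model with both arms constrained to a common baseline mean. This form also keeps women who have a baseline value only.

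Do not use baseline as both outcome row and covariate. If the Women's Health Questionnaire domains are to be analysed with the two-point model, apply the same form to them. The article does not settle whether they are.

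The cost is a sentence or two of analysis wording. The ANCOVA form spends one degree of freedom. No new data or participants are needed, and the sample size is unchanged.

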#### Secondary outcomes

Secondary outcomes include the group difference between OLP and no-treatment in hot flush frequency, health-related quality of life, global improvement, and the number of responders (≥ 50% in hot flush frequency at 4 weeks from baseline) at post-treatment [47]. Hot flush frequency is assessed as part of the diary. Health-related quality of life is measured with the Women’s Health Questionnaire (WHQ) [48], a questionnaire of proven reliability and validity [49] which covers eight domains including depressed mood, somatic symptoms, memory/concentration, vasomotor symptoms, anxiety, sexual life, sleep, and attractiveness. Although part of the questionnaire, the menstrual symptoms scale is excluded from analyses since many patients would be post-menopausal. Patients indicate their global improvement of hot flushes on a seven-point Likert scale (1 ‘very much worse’, 2 much worse’, 3 ‘minimally worse’, 4 ‘no change’, 5 ‘minimally improved’, 6 ‘much improved’, 7 ‘very much improved’) of the Patient Global Impression of Change scales (PGIC) [50]. The PGIC is a validated and commonly used questionnaire in the field of pain and has been previously used in a sample with menopausal women [51].

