#### Missing data

To analyze diary data, we aggregate daily data so that each data point comprises a weekly mean (Fig. 2). Means are calculated if at least 3 days of the week are completed. Almost identical means of the hot flush diary were found for 3 and 7 days [66]. Missing data points are not replaced since, in linear mixed models, missing outcome data are handled using maximum likelihood estimation, assuming that data are missing at random conditional on information in the model. Single missing values in questionnaires are substituted by the mean of the remaining items, provided that 80% are completed [67].

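### Hot flush frequency is averaged into non-integer weekly means and then assigned a negative binomial count model, so the stated distribution does not fit the stated data

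*Protocol article*

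**What the plan says.** Under Missing data, the article sets one rule for all diary data: "we aggregate daily data so that each data point comprises a weekly mean". It adds that "Means are calculated if at least 3 days of the week are completed". Under Secondary outcomes, it states that "Hot flush frequency is assessed as part of the diary", so the averaging rule covers frequency.

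Under Efficacy, "the analytical strategy for all secondary outcomes corresponds with the one described for the primary outcome". That strategy uses weekly means ("Since each data point reflects a weekly mean, up to five weekly means are included for each participant"), a baseline covariate, an autoregressive residual structure and a random intercept per woman. The same section then classes frequency as a count: "for count outcomes (hot flush frequency), we use a negative binomial distribution with a log-link".

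The article does not exempt frequency from the averaging. It mentions no weekly total, offset for completed days or robust standard error, and it names no software or estimation method for this model.

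**The concern.** The negative binomial is a distribution on the integers 0, 1, 2 and so on, and its conditional variance cannot fall below its mean. A mean over three to seven days is usually fractional and varies much less than a single day's count. Three consequences follow.

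- **The analysis is not determined.** Software may reject fractional values, round them, or evaluate the likelihood formula where it is not a probability distribution. These choices need not give the same p-value.
- **Precision can be misstated.** The model is not scale-invariant: the same diary implies different precision when entered as a daily average or as a weekly total. If the variance floor binds, the standard error is too large.
- **Partial weeks carry full weight.** The number of days behind each mean never enters the model.

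What is at stake is the inference on one of four secondary outcomes, in a trial planned for 90 analysed women.

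**Working it through.** **The plan's own figure.** The article gives no figure for the frequency model. Its only calculation concerns the hot flush score (Power analysis). A two-sided t-test at 0.05 with d = 0.60 and 45 per arm has power 0.804, and 90/0.9 = 100. The sample size reproduces and does not depend on this point.

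**Inputs.**
- From the article: 3 to 7 days per mean; 45 analysed per arm; a planning score of 19 falling by 4, so a ratio of 15/19 = 0.79 (log −0.236), borrowed here as the frequency effect.
- Assumed: mean frequency μ = 9.5 a day (score 19 at mean severity 2), range 5–15; Poisson daily counts; a within-woman week-to-week coefficient of variation (CV) from 0 to 0.30.

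**Variance comparison.** The variance of a mean over D days is μ/D + (CV·μ)². The negative binomial allows no conditional variance below μ. At μ = 9.5 and CV = 0, the true variance is 9.5/7 = 1.36 for seven days and 9.5/3 = 3.17 for three, against a floor of 9.5.

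Floor divided by true variance, seven-day mean:

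| μ per day | CV 0 | CV 0.10 | CV 0.20 | CV 0.30 | Break-even CV |
|---|---|---|---|---|---|
| 5 | 7.00 | 5.19 | 2.92 | 1.69 | 0.41 |
| 9.5 | 7.00 | 4.20 | 1.91 | 1.00 | 0.30 |
| 15 | 7.00 | 3.41 | 1.35 | 0.67 | 0.24 |

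Break-even solves μ = μ/7 + (CV·μ)², so CV = √((6/7)/μ). Above it, the dispersion parameter can match the true variance and the floor no longer binds.

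**Partial weeks.** At μ = 9.5, a three-day mean has 3.17/1.36 = 2.3 times the variance of a seven-day mean at CV 0. The ratio falls to 4.07/2.26 = 1.8 at CV 0.10 and 11.29/9.48 = 1.2 at CV 0.30.

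**Effect on the group contrast.** The variance ratio does not carry straight through to the standard error, so the contrast was simulated. There were 100 trials per setting, 45 women per arm, four post-baseline weeks, log baseline as covariate and a random intercept. The between-woman log SD was 0.45 and the woman-level change log SD 0.20. There was no autoregressive term. Model SE is divided by the empirical SD of the week-4 log rate ratio; ranges cover the null and the 21% reduction. Power is for the 21% reduction.

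| CV | SE ratio, weekly mean | SE ratio, total with offset | Power, weekly mean | Power, total with offset |
|---|---|---|---|---|
| 0.10 | 1.24–1.27 | 0.95–0.99 | 0.89 | 0.96 |
| 0.20 | 1.07–1.08 | 0.96–1.00 | 0.79 | 0.86 |
| 0.30 | 0.99–1.03 | 0.98–1.05 | 0.64 | 0.69 |

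Monte Carlo error on power is about 2–5 points, so the direction is firmer than the size. With weekly means, the dispersion estimate sat at its lower bound (0.0001) at CV 0.10 and 0.20 and rose above it (0.016–0.020) at 0.30, which agrees with the break-even calculation. The mean estimates under the effect were −0.245, −0.235 and −0.243 against a target of −0.236: no material bias. Rejection under the null was 0.000, 0.050 and 0.030: no sign of excess type I error.

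**The case against.** **The inflation depends on the fitting method.** This is the strongest counter-argument. Secondary outcomes inherit an autoregressive residual structure, and generalized mixed models with such a structure are commonly fitted by pseudo-likelihood. That method accepts fractional values and can estimate a residual scale below 1. A separate simulation at mean 9.5 (seven-day means, 21% reduction, dispersion at its lower bound, 600 trials per setting) gave SE ratios of 1.01, 0.93 and 0.96 at CV 0.10, 0.20 and 0.30 with a free scale and autoregressive residuals. Without the residual term they were 1.31, 1.05 and 0.95. This stands: oversized standard errors are not a property of the plan as written. It also shows that the answer turns on an implementation choice that the article does not fix.

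**A much larger effect is tempting to infer.** A reader might conclude that the variance is simply too large, or that the standard error is √7 = 2.65 times too large. The arithmetic is right, but only for a pure change contrast between two time points with Poisson days and no week-to-week variation. The plan has up to five weekly means, a baseline covariate, a random intercept and a group comparison at post-treatment. The documents give no mean or variance for frequency that would place this trial below break-even.

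**Three-day and seven-day means are said to agree.** The article cites a source for this under Missing data. That supports the three-day minimum but says nothing about equal precision. Equal weighting does affect every weekly-mean outcome, so it is not peculiar to the negative binomial.

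**A condensed article leaves detail to the analysis plan.** That would excuse silence about an offset. Here the article states both the aggregation and the distribution, and the two do not fit together.

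**Conclusion.** The point holds in a limited form. Two stated rules are incompatible for hot flush frequency: the data are weekly means and the model is for integer counts. The analysis is therefore not determined by the text, and partial weeks are weighted as full ones.

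The effect on precision is conditional. It arises if the model is fitted by likelihood without a free residual scale and week-to-week variation is below a CV of roughly 0.24–0.41 (means of 15 down to 5 a day). In the main simulation the standard error was then up to about 27% too large, and nothing was left of this at CV 0.30. Power was about 5–7 points lower. Any such error is conservative. These sizes rest on assumed frequencies, Poisson days and assumed between-woman variation; the article's figures cannot narrow them. The effect estimate, the primary outcomes and the sample size are not affected.

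**What to change.** State that frequency enters the model as the weekly total number of hot flushes. Use a negative binomial mixed model with log link and an offset of log(number of completed diary days). Keep the three-day minimum and adjust for the log baseline daily rate. The group effect is then a ratio of daily rates on genuine counts, and partial weeks get the weight that their days support. In the simulation this brought the ratio of model SE to true SD to 0.95–1.05 in every setting.

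Exempt frequency explicitly from the weekly-mean rule under Missing data, so that the two sections agree. Women already record each flush in the diary (Primary outcomes), so no new data are needed. The cost is analysis-plan wording and minor programming.

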#### Sensitivity analyses

Sensitivity analyses include rerun of outcome analyses with missing values substituted using the last-observation-carried-forward method, per-protocol analyses (exclusion of patients who have discontinued treatment or reported adherence rates < 90%), analyses with adjustment for the variables ‘years of hot flushes’, and stress, and after exclusion of patients who have conducted lifestyle changes in the course of the study.

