## Methods/design

### Study design

In this randomized-controlled, assessor-blinded superiority trial, menopausal women with hot flushes are assigned 1:1 to a 4-week OLP treatment or a no-treatment control group. The control group allows for examining whether OLP has beneficial effects over and above spontaneous improvement and statistical phenomena. Patients receive three study visits at enrolment, baseline, and post-treatment (Fig. 1). Women allocated to OLP are randomized a second time at post-treatment to either another 4 weeks of placebo (OLP 8wk) or to discontinue the treatment (OLP 4wk). Accordingly, OLP 8wk and OLP 4wk receive a fourth study visit at 8 weeks follow-up, whereas, for the no-treatment group, the study ends at week 4. Two calls at weeks 2 and 6 are conducted to inquire about adverse events and adherence. To further understand the experiences of participants and potential psychological mechanisms from their perspective, qualitative interviews will be conducted with a subgroup of patients who have reported improvements under the placebo. Ethics approval is given by the Physicians’ Chamber of Hamburg (reference number PV5787). The trial is registered at ClinicalTrials.gov (ID NCT03838523) and complies with the SPIRIT guidelines [37].

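### The only missing-outcome sensitivity analysis named is last observation carried forward: one fixed, unlikely assumption that can shift the group difference and does not show how far missing at random could fail before the conclusion changes

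*Protocol article*

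**What the plan says.** Under Missing data, the protocol article leaves missing outcomes unimputed in the main analysis: "Missing data points are not replaced since, in linear mixed models, missing outcome data are handled using maximum likelihood estimation". The condition it attaches to this approach is missing at random, in the words "assuming that data are missing at random conditional on information in the model". The same section has a rule for questionnaires, "Single missing values in questionnaires are substituted by the mean of the remaining items", but that is a scoring rule for single items and does not deal with absent assessments.

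Under Sensitivity analyses, outcome analyses are rerun with "missing values substituted using the last-observation-carried-forward method". The other reruns listed there are a per-protocol analysis ("exclusion of patients who have discontinued treatment or reported adherence rates < 90" per cent), adjustment for years of hot flushes and stress, and exclusion of women who changed their lifestyle. None of these concerns missing outcomes.

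Two other sections bear on whether scores stay flat. Study design says the control group is there to examine "whether OLP has beneficial effects over and above spontaneous improvement and statistical phenomena". Power analysis expects "a four-point reduction in the hot flush score (frequency × severity) after 4 weeks of placebo". Under Efficacy, the composite score has up to five weekly means per woman. Bothersomeness has only a baseline and a post-treatment value.

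**The concern.** A sensitivity analysis for missing data should change the assumption in a plausible direction and show how much change the conclusion can bear. LOCF makes one departure from missing at random, no change after the last value, and does not vary it. That departure conflicts with the falls the protocol expects. For bothersomeness, a woman who leaves has no value after baseline, so she is assigned zero change.

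Dropout related to outcome is plausible. Women know their allocation, half receive no treatment, and worsening symptoms can lead to discontinuation (Blinding; Procedures). If dropout or the remaining fall differs by arm, LOCF moves the group difference by an artefact of its own. Disagreement with the primary result may then be that artefact, and agreement gives little assurance. Entering filled values as if observed also overstates the information in the data.

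**Working it through.** **Inputs from the protocol article.** Power analysis: "given a mean of 19, standard deviations of 10"; design effect d = 0.60, which is 6 points at SD 10; two-sided alpha 0.05; 90 evaluable women; 10% attrition; 100 randomised. Study design: 1:1 allocation.

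**Assumptions, because the article gives no figures.** Linear change over four weeks; a fall in untreated women of 2 to 4 points (8 as an extreme); the dropout split by arm; the time of dropout; a baseline-to-week-4 correlation of 0.6.

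**The plan's own figure.** By the noncentral t distribution at d = 0.60, 45 per arm gives power 0.804 and 44 per arm gives 0.795, so N = 90. Then 90 / 0.90 = 100. The sample size reproduces and is not in question.

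**Bias of LOCF in the week-4 difference.** Let F be an arm's fall by week 4, p its dropout share, and r the part of the fall still to come at the last observed value (T = OLP, C = control). LOCF estimates F_T(1 − p_T·r) − F_C(1 − p_C·r), so

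bias = r × (p_C·F_C − p_T·F_T).

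This is zero when falls and dropout are both equal. A fall in both arms is not enough to produce bias.

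| Scenario | Last value at week 2 (r = 0.5) | Last value at baseline (r = 1) |
|---|---|---|
| True 6 points, dropout 10% / 10% | 6 − 0.5×0.1×6 = 5.7 | 6 − 1×0.1×6 = 5.4 |
| True 6, OLP 15% / control 5%, control fall 2 | 6 + 0.5×(0.1 − 1.2) = 5.45 | 6 + (0.1 − 1.2) = 4.9 |
| True 6, OLP 15% / control 5%, control fall 4 | 6 + 0.5×(0.2 − 1.5) = 5.35 | 6 + (0.2 − 1.5) = 4.7 |
| True 6, OLP 5% / control 15%, control fall 4 | 6 + 0.5×(0.6 − 0.5) = 6.05 | 6 + (0.6 − 0.5) = 6.1 |

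If dropout is spread evenly, so that the last value is at baseline or week 1, 2 or 3, r averages (1 + 0.75 + 0.5 + 0.25)/4 = 0.625. The 10% / 10% case then gives 6 − 0.625×0.6 = 5.6. The 15% / 5% case with a control fall of 4 gives 6 − 0.625×1.3 = 5.2.

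A large-sample simulation (SD 10, dropout after week 2 depending on the week-2 score, hence missing at random) agrees: LOCF gave 5.70 to 5.72 at 10% / 10%. A regression estimator valid under missing at random, standing in for the likelihood analysis, stayed within 0.02 of the full-data value throughout.

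**No true effect, r = 0.625, OLP 5% / control 25%.**

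- 4-point natural fall: 0.625 × (0.25 − 0.05) × 4 = 0.5 points of false benefit.
- 8-point natural fall: 0.625 × 0.20 × 8 = 1.0 point.

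With 50 per arm and baseline adjustment, the standard error is 10 × √(1 − 0.6²) × √(2/50) = 1.6. The shifts are 0.31 and 0.63 standard errors. By the normal approximation the type I error is 0.0497 + 0.0115 = 0.061 for the first and 0.0909 + 0.0049 = 0.096 for the second, that is, about 6% and 10%.

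At OLP 5% / control 15% with a 4-point fall, the false benefit is 0.625 × 0.10 × 4 = 0.25 points and the type I error stays near 5%.

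**Bothersomeness (r = 1 for every dropout).** The article gives no SD or expected fall on this scale, so the bias is stated as a share. At 10% / 10% dropout the difference shrinks by 10%. With no effect, the false benefit is (p_C − p_T) times the natural fall: 10% of it at 15% control / 5% OLP, and 20% of it at 25% / 5%.

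**What LOCF leaves unexamined.** If 10% of OLP values are missing and are truly 5 to 10 points worse than assumed, the estimate moves by 0.10×5 = 0.5 to 0.10×10 = 1.0 points. The significance threshold is t(0.975; 88) × 10 × √(2/45) = 4.19 points unadjusted. With baseline adjustment it is 4.19 × 0.8 = 3.35. Against the stricter, unadjusted threshold, the penalty on OLP dropouts that removes significance is (6 − 4.19)/0.10, about 18 points, for an estimate of 6, but only (4.5 − 4.19)/0.10, about 3 points, for an estimate of 4.5. That second kind of result is where a tipping-point analysis is needed and where LOCF says nothing.

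**The case against.** The strongest reply is that LOCF does not carry the conclusion. The primary analysis is a likelihood-based mixed model on the intent-to-treat sample without imputation, which is sound under missing at random. LOCF is one supportive rerun among several. This stands, and it limits the weight of the point.

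A second reply is that the article is condensed, says only that the sensitivity analyses include those listed, and may be supplemented by an analysis plan that is not shown. That is fair against a complaint of mere absence. But LOCF is a named choice, and the choice itself is unsuitable here.

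Third, a reader might infer that LOCF ignores women who leave because they feel no benefit. The documents do not support that. LOCF holds such women at their last value, and for bothersomeness at baseline, which is close to that scenario. The fair criticism is that this departure is fixed, applied to every dropout whatever the reason, and never varied.

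Fourth, the false-positive figures rest on assumed extremes. Dropout of 25% against 5% averages 15%, above the planned 10%, and an 8-point fall in untreated women is twice the four points that Power analysis takes for placebo. This stands too: when the split averages 10%, the false benefit is about 0.25 points.

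**Conclusion.** The point holds as a weakness of the sensitivity analysis, not of the primary analysis. LOCF imposes a single assumption at odds with the course the protocol expects, and it cannot show how robust the result is to departures from missing at random.

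The size is modest. At 10% attrition in each arm, a 6-point effect is understated by 0.3 to 0.6 points. If dropout is unequal at the same average, the estimate runs from about 4.7 to 6.1. False benefits of 0.5 to 1.0 points, with type I error of about 6% to 10%, need the strongly unequal dropout assumed above. The fall in controls, the dropout split, its timing and the correlation of 0.6 are all assumptions.

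Two stronger readings are tempting and unsupported. One is that LOCF is biased whenever symptoms fall in both arms. Each arm's mean is biased, but the group difference is not if falls and dropout are equal; the superiority hypothesis, which implies unequal falls, is what makes bias likely. The other is that the trial's main result is unreliable; nothing here shows that. The change is still worth making because it is cheap and matters most if the result lies near the significance threshold.

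**What to change.** In Sensitivity analyses, replace LOCF for both primary outcomes with multiple imputation:

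- Impute missing post-treatment values from baseline and all available weekly diary values. Use the diary for bothersomeness as well, since its two-point model does not draw on it.
- Add a shift (delta) to the imputed values, varied separately in each arm. Increase it until the conclusion at two-sided 0.05 changes, and report that tipping point with a judgement on whether such a shift is plausible.
- Combine the imputed datasets so that the uncertainty of the imputed values enters the standard errors.

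Imputing OLP dropouts from the no-treatment arm's course is an optional addition. It is not sufficient alone, because it leaves dropout among untreated women unexamined.

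The primary mixed model and the sample size stay unchanged. The cost is a change of wording and some extra programming; no new data or visits are needed.
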